### **10.3 Blinding**

The cell therapy facility and clinical trials pharmacist will be unblinded. The unblinded individuals will keep the treatment information confidential and will not discuss or release information on treatment allocation to the patient, the investigator, or other members of the research team.

As in prior studies of MSCs (48, 66), the infusion bag containing either the cell product or placebo will be masked at the time of preparation in the clinical site's cell therapy facility so that the contents of the infusion bag are not visible to the investigators or to the clinicians who

are administering the study drug. The contents of the infusion bag will be administered through a masked infusion set.

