| 6 | How               | 
The REALIST ORBCEL-C substance will be thawed and re-suspended in Plasma-Lyte 148 in the clinical site's cell therapy facility by the cell therapy facility staff according to the Product Specification.
 
The cell therapy facility or site pharmacy staff will be responsible for preparing the Plasma-Lyte 148 placebo.
 
The study drug infusion should be commenced as soon as possible after delivery to site ICU and infusion completed within 6 hours of the start of the thaw procedure.
 
A single dose of the study drug will be administered intravenously over approximately 30 to 90 minutes.
 
Only 1 patient will be treated at a time. For the phase 1 trial, the CTU will manage the recruitment process and will communicate to sites when a patient can be recruited to ensure only 1 patient across all sites is treated at a time and that each patient will receive treatment no less than 24 hours following the completion of treatment of another patient. This does not apply to the phase 2 trial.
 
A single dedicated infusion line should be used for cell administration. The study drug can be infused via peripheral or central venous access, though if administered through a peripheral intravenous access, it should be at least 20-gauge, and ideally 18-gauge. The cells are administered through a standard blood filter tubing set with a 170 to 260 micron filter.
 |

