## 11.2 Study Drug Supply

National Health Service Blood and Transplant (NHSBT) will manufacture REALIST ORBCEL-C and distribute it to each of the cell therapy manufacturing facilities. The cell therapy manufacturing facilities will thaw and further dilute REALIST ORBCEL-C to produce the final infusion solution for administration to the patient. Victoria Pharmaceuticals will manufacture the placebo solution for infusion (Plasma-Lyte 148) and distribute it to each of the cell therapy facilities. The IMP will be labelled in accordance with regulatory requirements. Trial guidelines will provide detailed information regarding the protocol for storage, thawing, preparation of final infusion solutions, labelling and administration of REALIST ORBCEL-C or Plasma-Lyte 148 placebo solution.

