### 12.2 Study Visits and Procedures

#### Day 0 (Baseline)

Baseline data (day 0) is the 24 hours preceding the time of recruitment which is defined as the time of study drug administration. If more than one value is available for this 24-hour period the value closest but prior to the time of study drug administration will be recorded. Day 0 (baseline) data collected will include but is not limited to:

- Patient demographics
- Date of birth, gender, height, weight, PBW
- ICNARC Case Mix Programme (CMP) number or equivalent
- Date and time of ICU admission
- Date/time of onset of mechanical ventilation
- Date/time of consent and enrolment (phase 1) or randomisation (phase 2)
- Aetiology of ARDS
- The Acute Physiology And Chronic Health Evaluation score II (APACHE II)
- First qualifying P/F ratio (including date/time)
- Worst P/F ratio (including date/time)
- Murray Lung Injury Score
- Determinants of the SOFA score
- Temperature
- Ventilation parameters including but not limited to: Mode of ventilation, minute volume, RR, mean airway pressure, plateau pressure, PEEP
- Arterial blood gas including but not limited to FiO2, PaO2, PaCO2, pH, lactate
- Oxygenation Index
- Use of adjunctive therapies
- Renal replacement therapy
- Clinical laboratory assessments: renal, liver function, ferritin and CRP, haematological and coagulation parameters where possible
- Blood for anti-HLA antibodies will be collected where possible
- Echocardiography parameters (during phase 2 study only) including but not limited to ventricular size and function and tricuspid annular plane systolic excursion (TAPSE) will be collected where possible.
- Clinical or PCR diagnosis of COVID-19

Baseline blood, urine and BAL for translational studies will be taken (where possible) prior to study drug administration. Sampling procedures are outlined below.

## Day 1

Day 1 is from the time of recruitment (study drug administration) to the end of that calendar day. If more than one value is available for this period, the value closest but after the time of administration will be recorded. The following data will be recorded:

- Date/time of expiry of the study drug.
- Date/time of commencing the infusion of the study drug.
- Date/time of completion of infusion of the study drug.
- Study drug administration.

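### Table 1 lets site pharmacy prepare placebo, a route the cells can never take, in conflict with the masking arrangement in section 10.3

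*Protocol*

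**What the plan says.** Four places in the protocol bear on who handles the bag and where.

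- **Section 11.1, Table 1, item 6.** The cells are "thawed and re-suspended in Plasma-Lyte 148 in the clinical site's cell therapy facility by the cell therapy facility staff". For placebo the wording differs: "The cell therapy facility or site pharmacy staff will be responsible for preparing the Plasma-Lyte 148 placebo". The same item asks for "infusion completed within 6 hours of the start of the thaw procedure", written for the study drug infusion without separating the arms.
- **Section 10.3.** The blind rests on concealment at preparation: "the infusion bag containing either the cell product or placebo will be masked at the time of preparation in the clinical site's cell therapy facility". On who knows the allocation, it says "The cell therapy facility and clinical trials pharmacist will be unblinded", and these people may not pass the allocation on to the patient, the investigator or the research team.
- **Section 11.2.** The placebo manufacturer is to "distribute it to each of the cell therapy facilities". Pharmacy is not named as a destination. Labelling and preparation details for both products are left to trial guidelines.
- **Sections 11.4 and 12.2 (Day 1).** The infusion must finish before the expiry on the product label, and the Day 1 data include "Date/time of expiry of the study drug".

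**The concern.** A blind that depends on a masked bag and masked tubing hides the contents. It does not hide where the bag came from. If one arm may be supplied from two units and the other from only one, the extra unit is informative: a bag known to come from it can only be placebo.

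This matters because several outcomes depend on the judgement of people at the bedside. A research team member is available during the infusion and for 5 hours afterwards (Table 1, item 5). The PI or a designee judges causality (sections 15.2 and 15.3). Under section 15.8, events in keeping with the underlying illness are not reportable unless the investigator links them to study drug or finds them unexpectedly severe or frequent. Suspicion about the arm could therefore change which events are counted, and the incidence of SAEs is the primary safety outcome (section 7.1). The oxygenation index, extubation and ventilator-free days also depend in part on ventilator settings and weaning decisions.

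**Working it through.** No figure in the plan is at issue, so the check is a comparison of the sections.

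1. **Preparation.** Cells: cell therapy facility only. Placebo: cell therapy facility or site pharmacy staff (both Table 1, item 6). The pharmacy option exists for one arm.
2. **Masking.** Section 10.3 says that the bag with either product "will be masked at the time of preparation in the clinical site's cell therapy facility". If placebo is prepared in pharmacy, masking at the time of preparation cannot also take place in the facility. The two statements agree only if pharmacy staff do the work inside the facility, which neither section says. No masking step is described for pharmacy.
3. **Stock.** Section 11.2 sends placebo to the cell therapy facilities. Preparation in pharmacy would need an onward transfer that the protocol does not mention. This is a poor fit rather than a strict contradiction.
4. **People.** Section 10.3 names the clinical trials pharmacist as unblinded. Table 1 speaks more broadly of site pharmacy staff. The wider group may be meant to work under that pharmacist, but the text does not say so.
5. **Expiry.** The only stated time limit runs from the start of a thaw, a step that plain Plasma-Lyte does not have. The protocol gives no rule for the placebo label. It also does not say that the placebo expiry differs, and the limit is written for study drug in general.
6. **Possible extent.** Section 14.1 plans 30 placebo patients in each of two cohorts of 60, so 30 + 30 = 60 placebo patients out of 60 + 60 = 120. The share treated at sites that use the pharmacy route is not given. If that share is *p*, and if origin is always visible in ICU, 60 × *p* placebo patients are exposed: 0 at *p* = 0, 30 at *p* = 0.5 and 60 at *p* = 1. If origin is never visible, the number is 0 whatever *p* is.

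**The case against.** The strongest reply is that the protocol shows no actual leak. It nowhere says that blinded ICU staff can tell which unit issued a bag. The pharmacist is unblinded and bound to silence (section 10.3). Pharmacist and facility share accountability for study drug as a whole, without a split by arm (section 11.3), so the involvement of pharmacy need not look unusual to someone in ICU. The total volume is 200 mL in both arms (section 11). One can also read Table 1 as saying who prepares and section 10.3 as saying where, so that pharmacy staff working in the facility would satisfy both.

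Most of this stands, and it limits the point to a possible risk. It does not remove the inconsistency. Table 1 sets the facility and pharmacy side by side as alternatives, and the reading that reconciles them has to be supplied by the reader.

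A reader might go further and infer that placebo has no matching expiry, so that the label and the Day 1 record give away every patient at every site, or that placebo bags arrive sooner because nothing is thawed. The protocol supports neither. The label expiry applies to study drug without distinction by arm, its details are left to trial guidelines that may well match the two, and no preparation or delivery times are given for either product.

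**Conclusion.** The point holds in a limited form. Table 1, item 6 conflicts with section 10.3 and fits poorly with section 11.2, and it creates a supply route open to placebo only, with no masking described for it. Unblinding would follow only under two conditions that the protocol leaves open: that a site uses the pharmacy route, and that the bag's origin is visible in ICU. Under both, the placebo patients supplied that way could be identified. The possible extent runs from none to all 60 placebo patients, and nothing in the protocol narrows it, so it would be wrong to say that allocation is revealed in any stated proportion of patients.

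The expiry question is a gap in the wording, not an error: the basis for a placebo expiry is not stated, although the research team records the value. The inconsistency is certain and its effect is not. What justifies the change is that it costs little and protects outcomes that rest on investigator judgement.

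**What to change.** In Table 1, item 6, delete the reference to site pharmacy, so that placebo is prepared and masked in the cell therapy facility like the cells. This brings the item into line with section 10.3 and with the delivery of placebo stock in section 11.2.

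Add one sentence, in section 10.3 or 11.4, that the labelled expiry recorded on Day 1 is set the same way for both arms.

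The cost is the loss of pharmacy as a back-up for placebo. That loss is small, because the facility already receives the placebo and must in any case be able to prepare cells for any randomised patient. The Day 1 expiry field can stay where it is: with a common rule it reveals nothing, and it documents compliance with section 11.4 and with study drug expiry as a termination criterion in section 11.5. No artificial delay for placebo bags needs to be prescribed.

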## 11.2 Study Drug Supply

National Health Service Blood and Transplant (NHSBT) will manufacture REALIST ORBCEL-C and distribute it to each of the cell therapy manufacturing facilities. The cell therapy manufacturing facilities will thaw and further dilute REALIST ORBCEL-C to produce the final infusion solution for administration to the patient. Victoria Pharmaceuticals will manufacture the placebo solution for infusion (Plasma-Lyte 148) and distribute it to each of the cell therapy facilities. The IMP will be labelled in accordance with regulatory requirements. Trial guidelines will provide detailed information regarding the protocol for storage, thawing, preparation of final infusion solutions, labelling and administration of REALIST ORBCEL-C or Plasma-Lyte 148 placebo solution.

## 11.3 Study Drug Accountability

The site clinical trials pharmacist and cell therapy facility staff will maintain full accountability for the study drug received, prepared and dispensed to patients in ICU. Records will be kept allowing traceability between the cell donor and the IMP recipient. Drug administration will be recorded on the patient's prescription chart.

## 11.4 Study Drug Infusion

The study drug infusion will be commenced as soon as possible following delivery to clinical site. Infusion should be completed prior to the expiry date/time stated on the product label.

The study drug administration guideline will provide detailed information on drug administration.

## 11.5 Study Drug Termination Criteria

Study drug will be discontinued if one of the following is met:

1. Study drug related adverse event.
2. Study drug expiry.
3. Death or discontinuation of active treatment.
4. Request from PerLR or ProLR to withdraw the patient from the study.
5. Decision by the attending clinician on safety grounds.

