### **Mechanical Ventilation**

Ventilation according to the ARDSNetwork ARMA trial, which demonstrated a reduction in mortality using a tidal volume of 6 ml/kg PBW will be the standard of care [9]. Target tidal volumes will be  $\leq 6$  ml/kg PBW to maintain a plateau pressure  $\leq 30$ cmH2O. The recommended Positive End Expiratory Pressure (PEEP) will be based on the ARDSnet ARMA trial [9]. (See appendix 2)

Oxygenation will be titrated aiming for SpO2 of 88%-95% or PaO2 7-10kPa. Permissive hypercapnic respiratory acidosis aiming for a pH  $\geq 7.2$  is recommended.

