## **11.8 Management During the Study Drug Infusion**

In keeping with standard care of critically ill patients in ICU, patients will be continuously monitored. Guidelines for the management of events during the study drug Infusion are provided in appendix 3.

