## 14.2 Analysis Population

In phase 2 the primary analysis will be conducted on outcome data obtained from randomised participants who receive at least some of their randomly allocated treatment. It is possible that some subjects may not receive the full treatment dose. Therefore a secondary analysis will be undertaken on the population who receive the complete treatment dose. An additional analysis in the COVID-19 cohort will also be conducted on patients who have a confirmed PCR diagnosis of COVID-19. For the COVID-19 cohort even if an additional risk factor for ARDS co-exists, these patients will be included in the COVID-19 cohort. A patient will be analysed according to the cohort to which they were randomised. A priori defined subgroup analyses will be undertaken based on severity of inflammation as measured by plasma CRP and ferritin.

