## 15.3 Assessment of Causality

The PI or designee should make an assessment of causality, i.e. the extent to which it is believed that the event may be related to the study drug.

| Category    | Definition                                                                                                                                                                                  |
|-------------|---------------------------------------------------------------------------------------------------------------------------------------------------------------------------------------------|
| Definitely* | Temporal relationship of the onset, relative to administration of the product, is reasonable and there is no other cause to explain the event, or a re-challenge (if feasible) is positive. |
| Probably*   | Temporal relationship of the onset of the event, relative to the administration of the product, is reasonable and the event is more likely explained by the product than any other cause.   |
| Possibly*   | Temporal relationship of the onset of the event, relative to administration of the product, is reasonable but the event could have been due to another, equally likely cause.               |
| Unlikely    | Temporal relationship of the onset of the event, relative to administration of the product, is likely to have another cause which can by itself explain the occurrence of the event.        |
| Not Related | Temporal relationship of the onset of the event, relative to administration of the product, is not reasonable or another cause can by itself explain the occurrence of the event.           |

\* Where an event is assessed as possibly, probably or definitely related, the event is an AR.

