| 
Hypersensitivity
 
Hypersensitivity to allogeneic plasma proteins.
                                                                                                                                                                             | 
 
• dyspnea
 
• hypotension
 
• fever
 
• urticaria
 
• tachycardia
 
• hypoxemia
 
                                                                                                                            | 
 
• Pause MSC infusion
 
• Check vital signs and O2 saturation
 
• Hydrocortisone IV 100-200 mg
 
• If severe adrenaline IV 1:10,000 50-100 microg (0.5-1ml).
 
• Increase supplemental O2 if O2 saturation is <93% and/or dyspnea
 
• Resume MSC infusion after reasonable resolution of signs and symptoms if considered safe to do so.
 
                                                                                                                                                 |
| 
Leukoagglutination
 
Because some leukocytes may be present in the MSC preparation (although MSC purity will typically be >95%), leukoagglutination symptoms may occur.
                                                                     | 
 
• cough
 
• “tickle in throat”
 
• dyspnea
 
• hypoxemia
 
• chest pressure
 
                                                                                                                                       | 
 
• Pause MSC infusion.
 
• Check vital signs and O2 saturation
 
• Increase supplemental O2 if O2 saturation is <93% and/or dyspnea.
 
• Resume MSC infusion after reasonable resolution of signs and symptoms.
 
                                                                                                                                                                                                                                                                                        |

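### Section 11.5 requires discontinuation for any study-drug-related adverse event, while Appendix 3 directs pause and resume for drug-related infusion reactions, and nothing says which governs

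*Protocol*

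**What the plan says.** Protocol section 11.5 opens with "Study drug will be discontinued if one of the following is met" and lists five criteria. The first is "Study drug related adverse event". The fifth is "Decision by the attending clinician on safety grounds".

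Section 11.8 then states: "Guidelines for the management of events during the study drug Infusion are provided in appendix 3". The first column of that appendix is headed as adverse reactions and has three rows: hypersensitivity, leukoagglutination and reactions to cryopreservatives. Each row begins with a pause and ends with resumption. The hypersensitivity row ends: "Resume MSC infusion after reasonable resolution of signs and symptoms if considered safe to do so". The cryopreservative row ends the same way. The leukoagglutination row directs resumption without the safety proviso.

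On what counts as drug-related, Table 3 in section 15.1 defines an adverse reaction as a response related to the product. The note to section 15.3 adds: "Where an event is assessed as possibly, probably or definitely related, the event is an AR".

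On analysis, section 14.2 takes as its primary population the randomised patients who received at least part of the allocated treatment. It adds that "a secondary analysis will be undertaken on the population who receive the complete treatment dose".

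**The concern.** A nurse or physician at the bedside needs one instruction when a patient reacts during the infusion. As written, the protocol gives two. A reaction judged at least possibly related meets a termination criterion in section 11.5, yet the appendix to which section 11.8 points says to pause and, once it has reasonably resolved, to carry on.

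Two things are at stake. The first is safety, which section 7 names as the primary focus of the phase 2 trial. The second is the make-up of the complete-dose population. The product is a single dose, and Table 1 (item 6) requires the infusion to be finished within 6 hours of the start of thawing. Terminating therefore normally forfeits the rest of the dose, while resuming may deliver it. Whichever page staff follow decides whether that patient counts as fully treated.

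**Working it through.** The point turns on the text, so the passages are set side by side.

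**Step 1: is 11.5 criterion 1 mandatory and unqualified?** The lead-in is mandatory. Criterion 1 has no qualifier for severity, seriousness or type. It does not read as discretionary either, because the clinician's safety judgement is a separate item (criterion 5).

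**Step 2: do the Appendix 3 events meet criterion 1?** Appendix 3 labels its events adverse reactions. By Table 3 that term means related to the product, and section 15.3 sets the threshold at possibly related. An event managed as one of these reactions and judged at least possibly related therefore meets criterion 1.

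**Step 3: compare the instructions.**

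| Reaction | Section 11.5, criterion 1 | Appendix 3 |
|---|---|---|
| Hypersensitivity | Discontinue | Pause; resume if judged safe |
| Leukoagglutination | Discontinue | Pause; resume (no safety proviso) |
| Cryopreservative reaction | Discontinue | Pause; resume if judged safe; stop for bradycardia with hypotension |

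The two texts agree in one scenario, bradycardia with hypotension. Otherwise they differ in all three rows.

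**Step 4: could discontinuing include pausing?** No text says so. Section 11.5 is headed as termination criteria, and the cryopreservative row of Appendix 3 itself separates a pause from a stop.

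**Step 5: which analyses can change?** The primary population requires only part of the treatment, so a patient whose infusion has begun is in it under either rule. The complete-dose population can change. Appendix 3 attributes the reactions to allogeneic plasma proteins, leukocytes in the cell preparation, and DMSO, whereas the placebo is Plasma-Lyte 148 (section 11). Terminations under 11.5 would therefore tend to fall on the cell arm.

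**Step 6: scale.** The protocol gives no reaction rate, so what follows is illustration only. Section 14.1 plans with a difference of 39, an SD of 51 and a two-sided 0.05 t-test. The standardised difference is 39/51 = 0.765. With 28 per group the power is 80.2%, which reproduces the stated 56 patients at 80%. Assume that k of the 30 cell-arm patients in a cohort leave the complete-dose analysis, that all 30 placebo patients stay, and that the planning values hold:

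| k removed | Groups | Power |
|---|---|---|
| 0 | 30 v 30 | 83.0% |
| 3 | 27 v 30 | 80.8% |
| 6 | 24 v 30 | 78.2% |

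The loss of power is small. The larger issue would be comparability, since patients would be removed after randomisation because they reacted, mostly from one arm.

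**Step 7: the saturation figures.** Section 11.7 says "Oxygenation will be titrated aiming for" an SpO2 of 88%-95% (or a PaO2 range). Appendix 3 raises oxygen at saturation below 93% and/or with dyspnea, in the hypersensitivity and leukoagglutination rows only. Saturations from 88% up to just below 93% are thus within the aim in one place and an action trigger in the other, with no linking text.

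**The case against.** The best defence is that Appendix 3 is the specific guidance and section 11.5 the general list, so the specific text implements the general one. Section 11.8 does send infusion events to the appendix, two of the three rows make resumption conditional on safety, and one scenario carries an explicit stop. Relatedness is also the investigator's judgement, so an event need not be judged related. This softens the conflict but does not remove it. No sentence gives the appendix precedence, and if 11.5 governs, the resume steps could never be followed for a reaction judged related. A separate study drug administration guideline (section 11.4) is not shown and may say more, but it would not cure a conflict inside the protocol.

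Four stronger readings are tempting and are not supported:

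- A reader might infer that sites do handle reactions differently. The protocol provides standardised training (Table 1, item 10). Divergence is possible, not shown.
- A reader might infer that an oxygen increase under Appendix 3 may by itself score as pre-specified infusion event 4 in section 15.8. That event needs both an FiO2 increase of 0.2 or more and a PEEP increase of 5 or more, so raising oxygen alone does not score it under either saturation figure.
- A reader might call the two saturation figures a plain contradiction. The lower limit in section 11.7 belongs to a general ventilation aim, and the Appendix 3 figure can be read as specific to an acute reaction. The protocol does not say so, which makes this a request for clarification.
- A reader might ask section 14.2 to define how a paused and resumed infusion is classed. If the whole dose is delivered, it is already a complete dose in plain words, and finer rules belong in the statistical analysis plan.

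**Conclusion.** The contradiction stands. An infusion reaction judged at least possibly related meets a mandatory termination criterion in section 11.5 and a pause-and-resume instruction in Appendix 3, for all three listed reaction types except the one scenario with an explicit stop. No text settles precedence.

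The consequence is a safety instruction that cannot be followed as written, together with an uncertain secondary complete-dose population. The primary analysis population and the sample size are unaffected. The size of the effect on the secondary analysis is unknown because no reaction rate is given. The expectation that it would fall mainly on the cell arm rests on the causes named in Appendix 3, not on data. The saturation figures are a minor point alongside.

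**What to change.** The sponsor should reconcile section 11.5 criterion 1 with Appendix 3 so that a single rule governs when an infusion reaction leads to termination and when to pause and resume, and should notify sites. This review does not say which rule is right. In the same amendment, the sponsor should either reconcile the Appendix 3 oxygen trigger with the section 11.7 aim or state why they differ. The cost is protocol wording and a site notice. No change to design, sample size or primary analysis is needed.
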